## **Supplement Trial Protocol**

This supplementary file includes the original study protocol, details of any amendments, and the trial registration record on the Australian New Zealand Clinical Trials Registry (ACTRN12623000603617).

## BACKGROUND

Patient education improves outcomes for people with low back pain. There is high quality evidence that written or verbal patient education can reassure patients and reduce subsequent healthcare utilisation in the short- and long-term. It is the most common recommendation in international clinical guidelines for back pain. Yet primary care clinicians globally appear to underuse patient education.

Easily accessed, evidence-based fact sheets, that can be printed or emailed to patients, could be a simple option to improve care for low back pain. A Cochrane review found patient-mediated interventions, including access to written patient materials, may improve the appropriateness of care for mixed conditions, though the evidence was uncertain. Fact sheets that help patients prepare for decision-making about their treatment options could encourage shared decision-making and better care.

Digital health companies now provide consultation software add-ons that provide access to fact sheets during a consultation. SMS systems allow clinicians to routinely send fact sheets following a consultation. Two new fact sheets being implemented using these approaches in Australia in 2023 are the *JAMA Patient Page* (JAMA fact sheet) and the *Australian Commission for Healthcare Safety and Quality Information for Patients Fact Sheet* (ACHSQ fact sheet). Both resources are evidence-based but differ in their focus. A key difference is that the JAMA fact sheet focuses on listing evidence-based treatment options, whereas the ACHSQ fact sheet explains how a person can self-manage back pain.

There is no rigorous evidence on the effects of either of these new resources among people seeking care for low back pain. It is uncertain whether a fact sheet resource that focuses more on listing medical management options (JAMA fact sheet), can increase a patient's preparedness for decision-making, compared with a resource that focuses on self-management.

High-quality primary care-based studies on fact sheets and other patient information materials require an adequate response rate. Identifying methods to boost recruitment, such as different survey advertising methods (eg, reimbursement incentives and appeals to

---

 Traeger AC, et al. *Bull World Health Organ.* 2019;97(6):423-433.


 Fønhus et al. *Cochrane Database Syst Rev.* 2018 Sep 11;9(9):CD012472.

social goods) could optimise research in electronic and postal questionnaires. It is unclear which strategies can improve the recruitment of patients with back pain attending primary care who have received a fact sheet.

## AIMS

Our primary aim is to compare preparation for decision-making among people seeking care for low back pain who are given one of two fact sheets. Secondary aims are to understand recruitment processes and engagement with research fact sheets, examine management intentions, feelings of reassurance about serious pathology and the acceptability of the fact sheets to people seeking care for low back pain.

## METHODS

### Consumer involvement

Our consumer partner [name] explained to the research team the value of receiving high-quality information about low back pain from one's GP. [name] helped us design our patient survey and suggested we document whether patients recalled their GP explaining the content of the fact sheet.

### Design, participants, and setting

This will be a survey of people receiving one of the two fact sheets. Around 790 patients who have recently seen their GP for back pain will be surveyed. Participants could receive a fact sheet via one of three methods. The first method is directly from their GP who prints and/or emails the sheet to their patient (GP-led access, Figure 1). The GP determines which sheet they will provide and so receipt of the JAMA or ACHSQ fact sheet is non-random.

[figure not shown]

**Figure 1.** GP-led access to back pain fact sheet. Appearance of the HealthShare sidebar where GPs can access fact sheets that are relevant to what is typed into consultation software. A clinician can print or email the sheet to their patient as they wish.

The second method is patient-led access to a back pain fact sheet via an SMS system called BetterConsult. BetterConsult invites a patient to receive a back pain fact sheet after they see their GP (Figure 2). Whether the patient receives the JAMA or ACHSQ fact sheet is determined randomly by the fact sheet distributor, HealthShare. Patients can view the sheet on their smartphone or print the sheet out and their GP will be notified. GPs can open and

discuss the fact sheet with their patient during the consult if they wish. Twenty-four hours after their consultation with the GP, HealthShare sends patients an SMS containing a link to the fact sheet.

[figure not shown]

The image shows a digital form with a white background and a thin black border. On the left side, there is a vertical purple bar. To the right of this bar, the text reads: "HealthShare offers a Low Back Pain Patient Information Fact Sheet. Would you like this to be sent to you via SMS after your appointment?". Below this text, there are two purple rectangular buttons. The left button is labeled "Yes" and the right button is labeled "No".

**Figure 2.** Patient-led access to back pain fact sheet. Patient opts to receive a fact sheet via SMS when they complete their details in a pre-consultation tool (BetterConsult).

The third method is via an advertisement on social media (Facebook, Twitter, and Instagram). The advertisement will invite people who have recently seen their GP for back pain to view a fact sheet and complete a short survey (See Appendix A).

The nature of the first two access methods means that we can make a randomised comparison of the survey responses to the two fact sheets delivered via patient-led access, but not those delivered by the GP-led access, ie in the consult by print or email. For people accessing the fact sheet via the third method (social media), the exposures will be randomised using Qualtrics software hosted by The University of Sydney. Data from patients receiving a fact sheet using the three methods (GP-led access vs Patient-led access vs Social Media) will be analysed separately in a sensitivity analysis.

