## Statistical analysis

Our primary analysis will compare the PrepDM scores in people exposed to the JAMA fact sheet vs the ACHSQ fact sheet, immediately after they have read the sheet. Assuming a mean difference of 6 points on a 100-point scale (ie 60 points in JAMA fact sheet group, 54 points in ACHSQ group, SD of 26) with 90% power, we require a sample size of 790. To account for anticipated uneven group size we will increase the minimum sample size to 1000.

For the secondary outcomes of management intentions, reassurance, and acceptability, we compare means and proportions where applicable in the whole sample and generate 95% confidence intervals.

---

 Western Sydney University. Human Research Ethics. Guidance on Reimbursements. 2020.

 Dhand, N. K., & Khatkar, M. S. (2014). Statulator: An online statistical calculator. Sample Size Calculator for Comparing Two Independent Means. Accessed 8 May 2023 at <http://statulator.com/SampleSize/ss2M.html>

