### Subgroup analysis

We will compare the effects of the sheets on PrepDM scores in people with chronic pain vs acute pain, and in people with higher pain intensity vs lower pain intensity. We will also examine effects on healthcare intentions in people who received the fact sheet through GP-led approach vs patient-led approach.

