| Update                                                                                             | 
This study is quasi randomised. Participants are allocated to intervention and control groups via three methods. The first method is based on GP discretion as to which study fact sheet they provide to their patient. The comparison of outcomes for people allocated to fact sheet interventions via this method is therefore non-random. The second allocation method is random. Based on a computerised random number list, a GP software provider will allocate access to either the intervention or control fact sheet, for one month at a time for the duration of the trial. The comparison of outcomes for people allocated to interventions via this method is therefore based on a randomised computer generated sequence.
 
The third allocation method will be random. Participants via social media advertisement will be allocated to either intervention or control fact sheet randomly.
                                                                                                                                                                                                                                                                                                                                                                                         |

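### The primary PrepDM comparison takes GP-chosen recipients together with randomised ones, which leaves the headline result open to confounding of unknown size

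*Supplement*

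**What the plan says.** The latest protocol describes the routes under Design, participants, and setting.

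- **GP-led:** "The GP determines which sheet they will provide and so receipt of the JAMA or ACHSQ fact sheet is non-random".
- **Patient-led SMS:** "Whether the patient receives the JAMA or ACHSQ fact sheet is determined randomly by the fact sheet distributor, HealthShare". The registry record (Study design, sequence generation) adds that the software provider will "allocate access to either the intervention or control fact sheet, for one month at a time for the duration of the trial".
- **Social media:** "the exposures will be randomised using Qualtrics software hosted by The University of Sydney".

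The same section accepts that GP-led recipients cannot contribute to a randomised comparison.

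Under Statistical analysis, the primary comparison carries no restriction by route: "Our primary analysis will compare the PrepDM scores in people exposed to the JAMA fact sheet vs the ACHSQ fact sheet". For the secondary outcomes, "we compare means and proportions where applicable in the whole sample and generate 95% confidence intervals". Separation by route is a sensitivity analysis in the protocol ("GP-led access vs Patient-led access vs Social Media) will be analysed separately in a sensitivity analysis"). The registry record likewise leaves the split between random and non-random allocation to a sensitivity analysis. The only other planned use of route is a subgroup analysis of "effects on healthcare intentions in people who received the fact sheet through GP-led approach vs patient-led approach", which concerns a secondary outcome.

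**The concern.** The registered hypothesis is causal: that one sheet raises preparedness for decision-making more than the other. The analysis meant to test it includes people whose sheet was picked by their clinician. Bias can enter in two ways.

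- **Selection within the GP-led route.** GPs may match the sheet to the patient, so GP-led recipients of the two sheets may differ before they read anything.
- **Unequal route mix.** If GPs favour one sheet, that arm holds more GP-led respondents. Any PrepDM difference between routes then shows up as a difference between sheets. The plan itself expects groups of uneven size, and GP preference is one possible source of that.

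The sample size is affected too. The target of 790, raised to 1000, counts all respondents, so the stated 90% power is not power for a randomised comparison. No rule says which result prevails if the pooled and the randomised estimates disagree.

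**Working it through.** **1. The plan's own figure.** Inputs from Statistical analysis: difference 6, SD 26, power 90%. Alpha is not stated for the main study; two-sided 0.05 is assumed.

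n per arm = 2 × (1.960 + 1.282)² × 26² / 6² = 2 × 10.507 × 18.778 = 394.6, so 395 per arm and 790 in total. This matches the plan exactly. The sample size arithmetic is sound.

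**2. Unequal route mix.** Assumptions, none of them in the documents: 1000 respondents, randomised routes split evenly, GPs choosing one sheet 80:20, GP-led patients scoring *c* points higher whichever sheet they get, and no true sheet effect.

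- Bias = *c* × (GP-led fraction of the favoured arm − GP-led fraction of the other arm)
- SE = 26 × √(1/n₁ + 1/n₂)
- Type I error = P(|Z + bias/SE| > 1.96)

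| GP-led share | Arms | *c* | Bias | SE | Bias/SE | Type I error |
|---|---|---|---|---|---|---|
| 5% | 40+475=515 vs 10+475=485 | 10 | 10×(40/515 − 10/485) = 0.57 | 1.645 | 0.35 | about 6% |
| 10% | 80+450=530 vs 20+450=470 | 10 | 10×(80/530 − 20/470) = 1.08 | 1.647 | 0.66 | about 10% |
| 30% | 240+350=590 vs 60+350=410 | 5 | 5×(240/590 − 60/410) = 1.30 | 1.672 | 0.78 | about 12% |
| 30% | 590 vs 410 | 10 | 10×(240/590 − 60/410) = 2.60 | 1.672 | 1.56 | about 34% |

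**3. Selection within the GP-led route.** Suppose GP-led respondents are a share *f* of each arm, and GP choice creates a spurious difference *b* among them. Then bias = *f* × *b*. With 500 per arm, SE = 26 × √(4/1000) = 1.644.

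- *f* = 10%, *b* = 3: bias 0.3, type I error about 5.4%
- *f* = 25%, *b* = 6: bias 1.5, about 15%
- *f* = 50%, *b* = 6: bias 3.0, about 45%

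**4. Power if only randomised respondents count.** For N randomised respondents, individually allocated 1:1, power = Φ(6 / (26 × √(4/N)) − 1.96).

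| GP-led share of 1000 | N randomised | Power |
|---|---|---|
| 0% | 1000 | 95.4% |
| 10% | 900 | 93.3% |
| 21% | 790 | 90.0% |
| 40% | 600 | 80.7% |
| 50% | 500 | 73.2% |

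These powers ignore clustering from month-level allocation on the SMS route, so they are upper figures.

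**The case against.** The plan does not hide the limitation. It says that GP-led receipt is non-random, the registry record calls the study quasi-randomised, and the route-specific analyses are prespecified. The randomised estimates will therefore be produced, and what is in dispute is which estimate carries the primary label. That stands, and it limits the harm. It does not protect the headline result.

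The GP-led share may also be small. The registry record says social media was added because the earlier methods were not bringing in enough participants. That remark covers the GP-led and SMS routes together, so it does not settle the GP-led share, but it is a good reason not to treat the 30% scenario as representative.

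GP explanation of the sheet does not cleanly separate the routes either, since GPs may also open and discuss it with SMS patients. A route gap is possible but not established.

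Pooling for the primary outcome is inferred: the explicit whole-sample wording belongs to the secondary outcomes. The inference is still the natural one. If the primary analysis were already confined to randomised routes, separating the routes would not be a sensitivity analysis. No separate analysis plan is shown, so nothing is made here of missing detail on covariate adjustment.

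Finally, the SMS route is less clean than individual randomisation, because sheets are allocated by the month. This is correct, and the remedy has to allow for it.

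**Conclusion.** The point holds as a risk to the primary inference. Followed as written, the plan puts non-randomised and randomised recipients into one primary contrast, although its own text says the former cannot support a randomised comparison.

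A reader might infer that the headline result is confounded, or that its false-positive rate is about 34%. The documents support neither. That figure needs 30% GP-led respondents, an 80:20 preference and a 10-point route gap, all assumed. Across the unequal-mix scenarios the type I error runs from about 6% to 34%, and a small GP-led share gives little bias.

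Nor do the documents show that the trial is underpowered for a randomised comparison. With individual 1:1 allocation, 90% power survives within 1000 respondents as long as GP-led respondents are at most 21%. It falls to about 81% at 40% and 73% at 50%. Monthly allocation on the SMS route could lower each of these figures by an amount that the documents do not allow one to calculate.

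**What to change.** - **Primary analysis:** allocated JAMA versus ACHSQ sheet among respondents from the two randomised routes, stratified or adjusted by route. The SMS part should be analysed so as to account for month-level allocation; a route term alone does not do this. The protocol and the registry record should describe the SMS allocation in the same way.
- **Secondary outcomes:** use the same set for comparisons between sheets.
- **GP-led recipients:** report them as a separate non-randomised comparison, adjusted for the age, sex, ethnicity, pain duration and pain intensity already collected. The pooled whole sample becomes a sensitivity analysis.
- **GP-led versus patient-led subgroup:** label it descriptive, since it sets a non-randomised contrast beside a randomised one.
- **Sample size:** count only randomised respondents toward the 790, or restate power for the number obtained, with allowance for monthly allocation.

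The cost is mainly wording in the protocol and registry record. Route is already asked in the fidelity item, and social media responses sit on a separate survey platform. The downside is that GP-led respondents leave the primary analysis, and the stated power may have to be lowered, or recruitment extended to keep it.

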### **Procedure**

Participants will be people >18 years visiting their GP for back pain who receive a back pain fact sheet and who choose to complete the online survey. Patients who access the survey link and agree to participate in the study will provide clinical and demographic details via an online form (age, sex, ethnicity, duration of back pain, pain intensity). No data from a participant's medical record will be used in this study.

COPYRIGHTED MATERIAL REDACTED

**Figure 3.** Potential participants can access the survey via a QR code on printed/emailed sheet or via clickable link on the fact sheet page or via social media advertisements.

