[options: most / some / a little]
  - How would you rate the length of the fact sheet?  
[options: much too short / a little too short / just about right / a little too long / much too long]
  - How much of the information in the fact sheet was new to you?  
[options: all / most / some / none]
- The fact sheet talked about different ways to manage back pain. It mentioned **medical care (pain medicines, imaging, surgery)** and **non-medical care (massage, heat, staying active)** for back pain. Did you feel the fact sheet was: [options: leaning very much towards medical care/ leaning a bit towards medical care/Balanced/ Leaning a bit towards non-medical care/Leaning very much towards non-medical care]
- How strongly do you agree or disagree with each of the following statements.  
[options: strongly agree / agree / neither agree nor disagree / disagree / strongly disagree]
  - I found the information in the fact sheet clear and easy to understand.
  - I would recommend this fact sheet to other people who are considering their options to treat low back pain.
- Fidelity
  - How did you receive the fact sheet
    - From my GP
    - Via SMS from my GP practice
    - Social media
    - Other [please describe]
- Implementation

---

 Traeger AC et al. JAMA Neurol. 2019 Feb 1;76(2):161-169.

- We will also conduct semi-structured interviews and or focus groups (depending on feasibility) with up to 20 clinicians and 20 patients (interview only) to identify barriers and facilitators to implementation of the fact sheets in primary care. We used the COM-B framework to create our initial interview guide (Appendix D) which will be updated iteratively as interviews/focus groups progress. For the clinician focus groups if feasible, we will conduct up to 3 focus groups with 5-6 GPs in each group.
- Recruitment rates
  - Proportion of people exposed to the survey advertisement who consent to participate

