### Consent

Participants will access the survey via a QR code on a printed/emailed sheet, via a clickable link on the fact sheet page, or via a link in a social media advertisement. Once they click the link or scan the QR code, participants will be taken to an invitation page summarising the study, with a link to the full PIS which they can download. Those interested in proceeding will complete a digital version of the PCF. Only those clicking 'Yes' to on the digital PCF can access the survey.

GPs who agree to participate in an interview or focus group will receive a link to the participant information sheet and online consent form prior to the interview/focus groups.

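### In the GP-led and SMS routes people consent after receiving their sheet, yet the pooled primary comparison names no adjustment and response is not counted by sheet

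*Supplement*

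**What the plan says.** All references are to the latest protocol in the Supplement.

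- **Entry to the study.** The Consent section states: "Participants will access the survey via a QR code on a printed/emailed sheet, via a clickable link on the fact sheet page", and then adds a link in a social media advertisement as a further way in. The consent form follows the link: "Only those clicking 'Yes' to on the digital PCF can access the survey". The caption of Figure 3 says the same of the sheet-based routes: "Potential participants can access the survey via a QR code on printed/emailed sheet or via clickable link on the fact sheet page", and it too goes on to mention social media.
- **Who is analysed.** Participants are patients "who receive a back pain fact sheet and who choose to complete the online survey".
- **Allocation.** The GP chooses the sheet in the GP-led route, and the distributor allocates it at random in the SMS route. For social media, "the exposures will be randomised using Qualtrics software hosted by The University of Sydney".
- **Data collected.** Consenting participants "will provide clinical and demographic details via an online form (age, sex, ethnicity, duration of back pain, pain intensity". No medical record data are used.
- **Primary analysis.** "Our primary analysis will compare the PrepDM scores in people exposed to the JAMA fact sheet vs the ACHSQ fact sheet". No model or covariate is named. The three routes are analysed separately only as a sensitivity analysis.
- **Response.** The recruitment outcome is "Proportion of people exposed to the survey advertisement who consent to participate". The nested study reports it by trial period, meaning the advertising period.

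**The concern.** In the two HealthShare routes the allocated sheet can influence who responds. If one sheet puts off its less engaged readers, those who remain may score higher on PrepDM whatever the sheet did for them. Randomising the SMS sheet makes the recipients comparable, but not the respondents.

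Pooling adds a second problem. GP-chosen sheets enter the primary contrast, so the mix of routes may differ between the two sheet groups, and PrepDM may differ between routes for reasons unrelated to the sheet.

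No stated analysis addresses either problem in the pooled estimate. Results by route show whether routes disagree. They do not adjust the primary estimate, and they cannot show differential volunteering within a route.

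**Working it through.** **1. The plan's own figure.** Inputs from Statistical analysis: difference 6, SD 26, power 90%. Two-sided alpha of 0.05 is assumed, since none is stated for this comparison.

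n per group = 2 × 26² × (1.960 + 1.282)² / 6² = 394.7, rounded up to 395, so 790 in total. This matches the plan.

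**2. Imbalance in a measured factor (all inputs assumed).** The factor may be access route or a collected characteristic. Bias = imbalance between sheets × PrepDM difference across the factor. With 1000 participants at 1:1, SE = 26 × √(2/500) = 1.644. Type I error = Φ(−1.96 − bias/SE) + 1 − Φ(1.96 − bias/SE).

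| Imbalance | PrepDM difference | Bias | Share of 6 points | Type I error |
|---|---|---|---|---|
| 5 pp | 5 | 0.25 | 4% | 5.3% |
| 10 pp | 10 | 1.0 | 17% | 9.3% |
| 20 pp | 10 | 2.0 | 33% | 22.9% |
| 20 pp | 15 | 3.0 | 50% | 44.6% |

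Adjusting for the factor removes this kind of bias.

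**3. Volunteering tied to the score itself, in one arm only (assumed).** A logistic volunteering model was simulated at the 27% response rate given for the nested study. Odds ratios of 1.1, 1.2 and 1.3 per SD of PrepDM give bias of about 1.8, 3.4 and 4.9 points, and type I error of about 20%, 55% and 85%. Adjustment removes this only as far as the collected variables explain it.

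**4. Unequal response.** Borrow the nested study's 27% and 32% as if they were response rates for the two sheets. The excess share of respondents in the fuller arm is (0.32 − 0.27)/0.32 = 0.156. If those extra people differ by half an SD (13 points, assumed), bias = 0.156 × 13 = 2.0 points. The two rates were set for advertising messages, so this shows scale only. The selection it represents is on engagement, which is not measured.

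**5. Precision.** Power = Φ(6 / (26 × √(4(1 − R²)/790)) − 1.96), and effective N = 790/(1 − R²). The R-squared values are assumed.

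| R-squared | Power at 790 | Effective N | Gain in participants |
|---|---|---|---|
| 0 | 90.0% | 790 | – |
| 2% | 90.6% | 806 | 16 |
| 5% | 91.4% | 832 | 42 |
| 10% | 92.8% | 878 | 88 |

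These figures treat participants as independently allocated.

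**The case against.** Several objections have force.

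- **Social media is different.** A reader might infer that consent follows the sheet for everyone. The text does not support that. In this route the link is in the advertisement and leads to the invitation and consent form, and Qualtrics both randomises the sheet and hosts the survey. Consent therefore appears to come first, although the order is not spelled out and people can still break off after seeing the sheet.
- **The collected data cannot correct everything.** A reader might infer that the covariates would allow full correction. They exist only for people who consent, so they cannot describe decliners or support weighting for non-consent. Counts by sheet are not planned, and no way of counting people handed a printed sheet is described.
- **The plan is silent on adjustment.** It does not declare the comparison unadjusted, and no separate analysis plan is shown in which a covariate set might appear. This stands against calling it an omission. It does not stand against improving the method that is stated.
- **Pain intensity is recorded after the sheet in the HealthShare routes.** Reading the sheet could change the rating, which calls for a sensitivity model without it.
- **Precision is not a reason to act.** Power is already 95.4% at 1000 participants with equal groups and no adjustment.

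The analysis by route is a partial safeguard: the social media estimate can be set beside the SMS estimate. It leaves the pooled primary estimate as it is.

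**Conclusion.** The point holds for the GP-led and SMS routes and for the pooled primary contrast. The collected characteristics and access route can remove measured imbalance between sheets. On assumed inputs that imbalance is worth 0.25 to 3.0 points, or 4% to 50% of the target difference. Nothing in the documents shows that the sheets do draw different respondents, so these figures show sensitivity and do not estimate the bias.

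It would go too far to conclude that the randomised comparison is invalid, or that adjustment would make it safe. Selection on engagement or on the score itself would be removed only in part, and some residual selection cannot be excluded. Equal consent proportions would be reassuring but would not prove its absence. The sample size of 790, raised to 1000, stands.

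**What to change.** 1. Make the primary estimate a linear model of PrepDM on sheet, adjusted for access route, age, sex, pain duration and pain intensity. Add a sensitivity model that omits pain intensity.
2. Report participant characteristics by sheet within each route.
3. Report the consent proportion by sheet in the SMS route, using the exposure counts that the nested study already needs. The registration record describes SMS allocation one month at a time, so monthly counts should map to sheet. In Qualtrics, report consent by sheet or, where consent precedes display, completion by sheet.
4. If these proportions differ, add a simple bounding analysis: the excess share of respondents multiplied by a stated range of PrepDM differences, as in step 4 of the working.
5. State that in Qualtrics consent and the baseline items come before the random sheet is shown.
6. Acknowledge that adjustment covers measured factors only, and that weighting for non-consent is not possible because nothing is recorded on decliners.

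The cost is a little more analysis, a request to the distributor for counts split by sheet, and possibly a change of page order in Qualtrics. No further participants or survey items are needed.
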